### **11.3 Statistical Analysis Plan**

Demographic, illness group (oncology, PICU, cardiac) and screener characteristics will be compared between groups. For parent-level data (for couples that were both eligible), categorical variables will be compared using Generalised Estimating Equation (GEE) models to account for within-couple correlation (with the exception of parent sex and illness group). A GEE with a Gaussian distribution will be employed to compare group means of the screening measure. Time between measurements using linear regression models, and illness group distributions will be compared using a chi-squared test.

GEE models will compare mean outcome measures between groups at T3, and GEE models will also account for within-couple correlations. Effect size Cohen's d will be calculated, and interpreted as small<0.2, medium>0.2-0.5, large=>0.5-0.8, very large >0.8 (Cohen, 1988).

Further analyses will include exploration of the predictors of intervention outcome, and a thorough analysis of treatment adherence, compliance with intervention and other process variables. Detailed descriptive analysis of pre-intervention child, parent and family characteristics will also be conducted to thoroughly explore the characteristics of families attending a parent focused, psychosocial intervention.

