### **3. STUDY OBJECTIVES**

#### **3.1 Primary Objective**

Does the “Take A Breath program lead to greater improvements in psychosocial distress than treatment as usual for parents of children with SCIs who report risk factors associated with the development of post traumatic stress symptoms in the first weeks following their child’s diagnosis.

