return written or online consent. If a parent requires the consent form to be mailed out again, or if an email consent form is preferred, then the form will be sent to the family once more, in another attempt to obtain written consent. If we again have difficulty obtaining formal written or online consent, a second verbal consent will be obtained over the phone prior to questionnaires being sent out and participation in the program commences. During this same phone call, a member of the research team will determine days and times that best suit the parent for attending a parent program and schedule them into a group. Parents allocated to the W-L arm will be advised when to expect the first set of questionnaires and advised of the approximate starting month for their participation in a group (following the completion of their post questionnaire).

- f. Pre-assessment measures will be distributed two weeks prior to the commencement of TAB group sessions to parents enrolled in the two treatment arms. Pre-assessment measures must be completed by parents prior to the commencement of the parent program. Parents have the choice to complete the questionnaires online or via paper/pen format.
- g. Any pre-assessment measures not returned/completed prior to the commencement of the parent program will be followed up. Parents allocated to the W-L arm will be followed up individually via their preferred method of contact. For those parents within the W-L arm that have failed to return written consent forms, another consent form will be sent with these pre-questionnaires, and they will be encouraged to return the signed consent forms when they return the pre-assessment measures.

Parents may choose to withdraw permission to participate at any time and request removal of their information from the database.

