#### Randomisation Procedures

Eligible parents will be randomised to either the parent intervention group or the W-L group. This will typically occur between three and four months post their child's diagnosis.

Three randomisation lists will be generated, one list per participating department. This will enable separate analysis by illness group as well as an overall exploration of outcomes for families of children with SCII. Each randomisation list will contain twenty six spaces. Participants will be randomly allocated to one of the two treatment arms using The RCH Department, Clinical Epidemiology and Biostatistics Unit (CEBU), computerised randomisation plan generator. This program will randomise each participant to one of the two treatment arms using the method of randomly permuted blocks. The end result will be two randomly allocated treatment arms of equal size divided between three randomisation lists organised according to Hospital Department (Cancer, Cardiac and PICU).

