#### 7.4 Blinding Arrangements

Research team members responsible for recruiting families to the study or delivering the TAB intervention to families will be blind to the randomisation list. No researcher involved with recruitment or clinical delivery will have access to the randomisation list, thereby ensuring they are blind to client allocation and ensuring the randomness of allocation. A research officer, not involved in either the recruitment process or clinical delivery, will manage the randomisation list. When a consent form is received the research assistant responsible for recruitment will contact the research officer to have the participant placed on the randomisation list for the correct department using their subject identification code.

The research assistant will be informed of the allocation and will then contact the parent to discuss the allocation and plan their enrolment in a group as described above.

Researchers conducting the data analysis will be blind to participant identity and allocation. Analysis will be conducted on re-identifiable data only. A research assistant not responsible for analysis will conduct a re-identification of participant if needed.

Participants will be partially blinded. That means that participating parents will know if they have been randomised to W-L or the parent intervention arm (TAB) once they have been advised whether they will receive the intervention immediately or in two-six months' time.

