## **11. STATISTICAL METHODS**

### **Sample Size Estimation**

In order to detect a difference of 6.0 (SD: 13.9) points (thought to be a clinically important difference in parents' experience of distress) in the Posttraumatic Stress Disorder Checklist (PCL- 5) measure, between the two treatment arms, with a significance level of 0.05 and power of 0.80, 82 participants will be required per arm. Allowing attrition, we therefore aim to recruit a total of 184

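### The outcome model in section 11.3 names no baseline distress score and no randomisation stratum, so precision is forgone, and its time label T3 does not match the post measure, T4

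*Protocol*

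**What the plan says.** The primary objective (section 3.1) asks whether the program will "lead to greater improvements in psychosocial distress than treatment as usual". Section 4.1 describes a pre-post control group design. Section 8.3 compares the arms at T2 (before the program) and T4 (after it), and Table 2 lists parent posttraumatic stress at both. In Table 2, T3 is the block of program sessions and has no outcome.

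Section 11.3 gives the outcome model as "GEE models will compare mean outcome measures between groups at T3". The only other feature it names is within-couple correlation. Illness group and screener scores appear in that section only as characteristics to be compared between arms.

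On stratification, the Randomisation Procedures state: "Three randomisation lists will be generated, one list per participating department". Allocation uses permuted blocks within each list.

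On timing, the ASDS is completed at screening (T1), within four weeks of diagnosis and before randomisation. The T2 questionnaire comes after allocation: "Pre-assessment measures will be distributed two weeks prior to the commencement of TAB group sessions to parents enrolled in the two treatment arms". Section 7.4 adds: "The research assistant will be informed of the allocation and will then contact the parent to discuss the allocation". The RCT recruitment steps also have wait-list parents told when to expect their first questionnaires. Parents would therefore ordinarily know their arm when they answer T2.

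**The concern.** A baseline measure of the outcome is usually its strongest predictor. If it is left out of the model, the variation it explains stays in the standard error, and any chance baseline difference between the arms carries through to the estimate. The protocol itself treats the pre-program score as predictive, since section 11.2 uses it to choose replacement values for missing post-program data. Leaving out a prognostic stratification factor has a milder effect: the standard error tends to be larger than it need be.

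Two further matters bear on the remedy. The time label in the model sentence points to a period with no outcome data. And the obvious covariate, T2 PCL-5, is self-reported after parents learn their arm, so hope or disappointment about the allocation could shift it differently in the two arms.

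**Working it through.** **Inputs.** From Sample Size Estimation: "In order to detect a difference of 6.0 (SD: 13.9) points", and "with a significance level of 0.05 and power of 0.80, 82 participants will be required per arm". The protocol also says "Allowing attrition, we therefore aim to recruit a total of 184". The analysed number is therefore taken as 82 per arm, 164 of 184 (1 − 164/184 = 10.9% attrition). The test is assumed two-sided, as the protocol does not say. The correlation ρ between T2 and T4 PCL-5 is not given; a range is assumed. Clustering by couple and by parent group is ignored throughout.

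**Step 1: the plan's own figure.** n per arm = 2·SD²·(1.960 + 0.842)²/δ² = 2 × 13.9² × 7.849/36 = 84.25, rounded up to 85. The stated 82 is about 3 short. At 82 per arm, SE = 13.9 × √(2/82) = 2.17 and power = Φ(6/2.17 − 1.96) = 78.9% (78.5% by the t-test). The stated size is thus close to that of an unadjusted comparison of two means.

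**Step 2: adjusting for T2 PCL-5.** The residual SD is 13.9 × √(1 − ρ²), and the variance falls by ρ².

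| Assumed ρ | Residual SD | SE at 82 per arm | n per arm for 80% power | Power at 82 per arm, normal (t-test) |
|---|---|---|---|---|
| 0 (unadjusted) | 13.90 | 2.17 | 85 | 78.9% (78.5%) |
| 0.3 | 13.26 | 2.07 | 77 | 82.6% (82.1%) |
| 0.5 | 12.04 | 1.88 | 64 | 89.1% (88.7%) |
| 0.7 | 9.93 | 1.55 | 43 | 97.2% (97.0%) |

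At ρ = 0.5 the variance falls by 25%, equivalent to 1/(1 − 0.25) = 1.33 times as many parents.

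**Step 3: weaker covariates.** If department, or any other covariate set, explains an assumed 2%, 5% or 10% of the variance, the residual SD is 13.9 × √(1 − R²) and power at 82 per arm is 79.7%, 80.9% or 83.0%. Screening ASDS may well sit in this range, because eligibility requires at least 9 on items 1 to 5 and at least 28 on items 6 to 19, which truncates its spread.

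**Step 4: chance imbalance.** Assuming the baseline SD is also 13.9, the chance difference in baseline means has SE 2.17 and a 95% range of ±1.96 × 2.17 = ±4.25 points. A difference at that limit moves the unadjusted estimate by ρ × 4.25: 1.3 points at ρ = 0.3, 2.1 at 0.5 and 3.0 at 0.7, against a 6-point target.

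**Step 5: the time label.** Section 11.3 says T3. Table 2 gives T3 to the sessions and T4 to the post-program questionnaires. T5 is for intervention families only. T4 is therefore the only time after the program at which the two arms can be compared.

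**The case against.** The strongest reply is that section 11.3 never calls the comparison unadjusted. That is read from the terms it lists, and a separate analysis plan could add covariates. Sections 4.1 and 8.3 speak of comparing the arms before and after the program, and the department lists are said to allow separate analysis by illness group. A reader might infer a settled decision to ignore baseline and department; the text supports only a model written without them. The point still stands as a pre-specification matter, because the protocol does fix the model class, the contrast, the time point and the one dependence handled.

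A reader might also infer that the planned estimate is biased, or that it contradicts the objective of greater improvement. Neither follows. Under randomisation the difference in post-program means estimates the difference in improvement without bias, and its standard error already covers chance imbalance. Leaving out the strata makes inference conservative rather than invalid.

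Nor does leaving out baseline put the trial below its plan, because the trial was sized as an unadjusted comparison. The loss is a gain not taken, and at a correlation of 0.3 that gain is under 4 percentage points of power.

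Finally, it is tempting to make T2 PCL-5 a primary covariate without conditions. The documents do not support that. If knowing the allocation shifts T2 differently by arm, adjusting for T2 can bring in a bias that the unadjusted comparison does not have. This objection stands and shapes the fix.

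**Conclusion.** The point holds as forgone precision plus a wrong time label, not as a flaw in validity. At 82 per arm, power is about 79% unadjusted, against about 82%, 89% or 97% with T2 adjustment at assumed correlations of 0.3, 0.5 or 0.7. Those gains belong to the T2-adjusted model. If T2 can serve only in a supporting analysis, the primary model with department and ASDS probably gains less, and the protocol has no figure to size it. The direction does not depend on the assumed correlation, but the amount does. Whether disclosure actually shifts T2 answers is not known from the protocol; the order of events only makes it possible. The change is worth making because every variable is already collected.

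**What to change.** 1. In section 11.3, replace T3 with T4 so that it agrees with section 8.3 and Table 2.
2. Pre-specify the primary model as a GEE of T4 PCL-5 on arm, department and screening ASDS, clustered by couple. Both covariates are fixed before randomisation.
3. Add T2 PCL-5 to the primary model only where T2 is returned before the parent is told the allocation. Otherwise report the T2-adjusted model as a pre-specified supporting analysis, with the timing stated. Settle which case applies before the unblinded analysis.
4. Use the same form for the secondary outcomes, each with its own T2 value under the same condition.

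The cost of items 1 to 4 is wording and a little more analysis. Delaying disclosure until T2 is returned is optional and not free. Parents are scheduled into groups during the enrolment call, and a group starts once at least five parents have been randomised to TAB, so feasibility depends on that scheduling. It may also come too late for some parents: section 4.1 gives a November 2014 start, and the PCL-5 description already reports internal consistency from this study.

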## 5. STUDY TREATMENTS

### 5.1 Treatment Arms

#### 5.1.1 Description

##### Program Structure

The parent intervention is a brief psychosocial parent mediated group program. It will consist of five sessions of 90 minutes duration each plus one additional sixth session (also 90 minutes) one month following the fifth session (totalling nine hours of contact time). The intervention will be delivered via an online videoconferencing platform called Google Hangouts <https://hangouts.google.com/> supported by the Royal Children's Hospital. This

program allows participants and practitioner/s to see and hear each other, including the option of presenting teaching materials on the screen. Participants are also able to send group emails and private emails to the practitioner if they chose to do so. Each participant will be sent an I-pad (set up for immediate use) for the duration of the program, programmed with Google hangouts, and specific instructions on how to login to the session. The I-pad will have internet access, with ample download capacity with Telstra to prevent disruption throughout this period. Internet access will be restricted to the Google hangouts application, limiting extraneous use of the internet. This process will ensure all participants have access to the technology and will minimise technical issues.

Voice recordings will be taken in each group, and used to assess program fidelity. To maintain privacy, participants will be requested to enter their first name only, which will be visible underneath their webcam image. An overview of the program's structure and content is provided in Appendix 11: TAB Program Outline.

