#### Program Adherence

The parent intervention groups will be facilitated by five mental health professionals (e.g., psychologists and therapists). The intervention is highly manualised and includes verbatim examples instructing facilitators on how to introduce key concepts during each session. Each session will contain a schedule outlining the strategies that must be covered during the session. To further ensure treatment fidelity the following strategies will be employed:

- Each session will contain an adherence checklist and facilitators are responsible for adhering to the checklist and completing it after each session.
- All facilitators will undergo extensive training in the delivery of the intervention. The training will include observing the sessions being delivered by the leading clinician, role playing session content and receiving feedback regarding the delivery of session content.
- Audio of the sessions will be recorded using the Google Hangouts program. The audio files will be stored on a password and firewall protected computer (on the hard drive) which can only be accessed by members of the research team. The taped sessions will be used to evaluate how the facilitators' perform in the session – e.g., their adherence to the program material, their clinical delivery skills etc. A team member will code aspects of the program to ensure treatment fidelity and to give an indication of inter-rater reliability.

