### **8.2 Parent Intervention Groups**

A total of 263 parents will participate in the main RCT study. It is anticipated that up to 30 parent groups will be delivered. A maximum of 10 parents will be enrolled into each group to ensure that parents can participate fully in all aspects of the program.

Parent groups will be scheduled on different days and times, with evenings and/or weekends being available. Sessions will be held once per week for a total of five consecutive weeks with a sixth session held two to four weeks later. The sixth session is included as it provides parents with a short period to practice and implement the skills and ideas taught during the program and to address any difficulties or barriers that arise when implementing them. All sessions will be delivered via online videoconferencing using Google Hangouts.

Parent programs will be commenced when enough parents have been randomised to the TAB treatment arm to constitute a group (a minimum of 5). Parents randomised to the Wait List arm will receive their pre questionnaires at the same time as the parents scheduled to commence that TAB group. In this way the timing for their assessment points will be matched to the participants in the TAB treatment arm.

Parents will be monitored by the practitioner facilitating the group they are attending throughout the intervention and at each assessment point. Evaluation questionnaires will be used to support the clinical judgment of the practitioner.

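### The primary model handles couples but not TAB therapy groups, so its standard error is too small if group delivery makes outcomes within a group correlated

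*Protocol*

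**What the plan says.** Parents are randomised individually, in permuted blocks by department, to give "two randomly allocated treatment arms of equal size divided between three randomisation lists" (Protocol, Randomisation Procedures).

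The two arms then differ in how care is delivered. Of TAB, the Program Structure section says: "The parent intervention is a brief psychosocial parent mediated group program". Section 8.2 starts a group once at least 5 TAB parents are available and sets an upper limit: "A maximum of 10 parents will be enrolled into each group". Under Program Adherence: "The parent intervention groups will be facilitated by five mental health professionals". The wait-list arm has standard hospital care and is offered TAB only after its post questionnaire (Treatment Arms), so its parents are ungrouped at the primary comparison.

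Section 11.3, headed as the statistical analysis plan, compares mean outcomes between arms by GEE and adds that "GEE models will also account for within-couple correlations". It mentions neither therapy group nor facilitator in the outcome model. Process variables appear only among further analyses. The sample size statement (section 11) has no ICC and no design effect.

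**The concern.** TAB parents share six sessions, the same fellow participants and the same facilitation. If these move outcomes, parents in one TAB group resemble each other more than parents in different groups. Correlation then exists in one arm only, which is a partially nested design. Clustering on couples does not absorb it, because couples sit inside therapy groups and different couples in the same group are still treated as independent.

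At stake is the precision claimed for the primary effect. The estimate itself is not biased by the omission, but its confidence interval would be too narrow, and the error runs in one direction for any positive group correlation.

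**Working it through.** **Inputs from the protocol.** Difference 6.0 and SD 13.9 on the PCL-5; alpha 0.05 (two-sided assumed, as the side is not stated); power 0.80; 82 per arm; 184 recruited in total; group size 5 to 10. **Assumed.** Therapy-group ICC ρ from 0.01 to 0.10, because the protocol gives none, and 8 per group as a value between the protocol's limits.

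**Step 1: the plan's own figure.** The protocol states "In order to detect a difference of 6.0 (SD: 13.9) points" and, "with a significance level of 0.05 and power of 0.80, 82 participants will be required per arm". With independent observations, n per arm = 2 × [13.9 × (1.960 + 0.842) / 6.0]² = 84.2, so 85. With 82 per arm the power is Φ(6.0 / [13.9 × √(2/82)] − 1.96) = 0.789. Thus 82 is slightly low on its own inputs but close. With 10% attrition, 82 / 0.90 = 91.1, so 92 per arm and 184 in total. No clustering allowance is hidden in these figures.

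**Step 2: variance under partial nesting.** Set couple correlation aside, since the GEE handles it, and take equal variances and m parents per TAB group:

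- Variance of the TAB mean = (SD²/n) × [1 + (m − 1)ρ]
- Variance of the wait-list mean = SD²/n
- Ratio of true to assumed variance of the difference: R = {[1 + (m − 1)ρ] + 1} / 2 = 1 + (m − 1)ρ/2
- True type I error = 2 × [1 − Φ(1.96/√R)]
- Power of a valid test at 82 per arm = Φ(6.0 / [13.9 × √(2R/82)] − 1.96)

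Example, m = 8 and ρ = 0.05: R = 1 + 7 × 0.05/2 = 1.175 and √R = 1.084. The assumed standard error is 13.9 × √(2/82) = 2.17 points, and the true one is 2.17 × 1.084 = 2.35. The type I error is 2 × [1 − Φ(1.96/1.084)] = 7.1%.

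**Step 3: the range.** Each cell gives R, true type I error, and power of a valid test.

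| ICC | 5 per group | 8 per group | 10 per group |
|---|---|---|---|
| 0.01 | 1.020; 5.2%; 0.78 | 1.035; 5.4%; 0.78 | 1.045; 5.5%; 0.77 |
| 0.02 | 1.040; 5.5%; 0.77 | 1.070; 5.8%; 0.76 | 1.090; 6.0%; 0.75 |
| 0.05 | 1.100; 6.2%; 0.75 | 1.175; 7.1%; 0.72 | 1.225; 7.7%; 0.70 |
| 0.10 | 1.200; 7.4%; 0.71 | 1.350; 9.2%; 0.66 | 1.450; 10.4%; 0.63 |

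At ρ = 0 the type I error is 5.0% and the power 0.789. The type I error depends on m and ρ, not on n.

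**Step 4: does couple clustering help?** A simulation (80 per arm, 8,000 runs per cell, sandwich standard errors clustered on couples; either no couples, or 40% of parents in couples with a couple correlation of 0.2) gave, at 8 per group, type I error of 0.072 at ρ = 0.05 and 0.093 to 0.102 at ρ = 0.10. The inflation remains. A sandwich clustered on therapy group without a small-sample correction still gave about 0.052 to 0.067 at ρ of 0.05 and 0.10.

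**Step 5: number of groups.** With 92 TAB parents, 92/10 = 9.2 and 92/5 = 18.4, so about 9 to 18 groups. That is few enough to need small-sample degrees of freedom.

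**The case against.** The strongest objection concerns what a null hypothesis means here. A reader might infer that a wholly inert program would be declared effective more than 5% of the time. The documents do not support that. Parents are randomised individually; if TAB changes no parent's outcome, the TAB arm is a random sample just like the wait-list arm. Scheduling its members into groups by availability leaves the variance of the arm mean unchanged, even if the parents scheduled together happen to be alike. Inflation needs group or facilitator effects that really move outcomes but average to zero. This stands, and it limits the claim to treatment-induced correlation.

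A reader might also infer that the type I error certainly exceeds 5%. With no ICC in the protocol, that is conditional, and at 0.01 the excess is negligible.

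On group size, 8 is not a protocol figure, and analysed groups will be smaller than enrolled ones. With the implied retention of 164/184, 8 enrolled is about 7.1 analysed, which gives 6.8% at ICC 0.05. At 3 analysed per group it would be 5.6%. This reduces the size but not the direction.

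On the number of groups, section 4.1 allows up to 30 per arm. Thirty groups of at least 5 need 150 parents, more than the 92 that follow from "Allowing attrition, we therefore aim to recruit a total of 184". Section 4.3, however, puts 184 families in each arm, which would allow 18 or more groups. The count of 9 to 18 therefore rests on the total of 184, which section 7.6 also uses.

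Finally, the wording of section 11.3 does not exclude further terms, and a separate analysis plan, not available here, could add one. But section 11.3 names the correlation to be modelled and omits the one that the intervention itself creates, so an analyst following it would leave that out.

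**Conclusion.** The omission is real: treatment is grouped in one arm, and the stated outcome model treats parents from different couples in the same therapy group as independent. The consequence is conditional. If delivery in groups induces a positive ICC, the standard error of the primary comparison is too small, by a factor of about 1.01 to 1.20 over ICC 0.01 to 0.10 and 5 to 10 per group, and a test of zero average effect has a true level of about 5.2% to 10.4%. These sizes rest on an assumed ICC range, equal group sizes and variances, and a two-sided normal test. The documents do not show that the ICC is above 0, and they give no reason to expect false positives from a program that affects nobody. Because the outcome analysis is the place to guard against this and the guard is cheap, section 11.3 should be amended before the data are analysed.

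**What to change.** Amend section 11.3 so that the primary outcome is analysed in one of two ways.

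- **Preferred:** a partially nested linear mixed model with a random intercept for therapy group in the TAB arm only, a couple random effect in both arms, and Satterthwaite or Kenward-Roger degrees of freedom.
- **If GEE is kept:** cluster on therapy group in the TAB arm and on couple (or single parent) in the wait-list arm, with a small-sample correction to the sandwich variance.

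For the intention-to-treat analysis, keep TAB parents who never attend in the group they were scheduled into. Treat those never scheduled as their own couple or singleton cluster.

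Make sure that a therapy-group identifier is held in the analysis dataset. The protocol schedules parents into groups and tracks their movement in its database but does not name such a field. Report the estimated group ICC. Outcomes by facilitator can be described, but five facilitators are too few to estimate a variance well.

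Cost: a change of analysis wording and one data field, with no new participants or visits. Intervals become somewhat wider. At 82 per arm the power of a valid test falls from 0.79 to between 0.75 and 0.77 at ICC 0.02, and to between 0.63 and 0.71 at ICC 0.10. That loss comes from the clustering itself; the present model would only hide it.
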